## Outcomes

| Table 1. Flowchart measurement               |                                              | Visit 0
Baseline                                                      | Visit 1
End of
intervention | Visit 2
Maintenance | Visit 3
Maintenance |
|----------------------------------------------|----------------------------------------------|--------------------------------------------------------------------------|-----------------------------------|------------------------|------------------------|
|                                              |                                              | Baseline                                                                 | Week 10                           | Week 35                | Week 75                |
| Primary outcome                       |                                              |                                                                          |                                   |                        |                        |
| Respiratory symptoms                         | COPD Assessment Test (CAT)                   | X                                                                        | X                                 | X                      | X                      |
| Secondary outcomes                    |                                              |                                                                          |                                   |                        |                        |
| Self-reported health questionnaires   |                                              |                                                                          |                                   |                        |                        |
| Anxiety and depression symptoms              | Hospital Anxiety and Depression Scale (HADS) | X                                                                        | X                                 | X                      | X                      |
| Quality of life – generic                    | EuroQoL-5D-3L (EQ-5D-3L)                     | X                                                                        | X                                 | X                      | X                      |
| Body pain- intensity and location            | Brief Pain Inventory (BPI)                   | X                                                                        | X                                 | X                      | X                      |
| Perceived mental and physical fatigue        | Multidimensional Fatigue Inventory (MFI-20)  | X                                                                        | X                                 | X                      | X                      |
| Sleep Quality                                | Pittsburg Sleep Quality Index (PSQI)         | X                                                                        | X                                 | X                      | X                      |
| Physical activity and function        |                                              |                                                                          |                                   |                        |                        |
| Physical activity                            | ActivePAL triaxial accelerometer (PAL)       | X                                                                        | X                                 | X                      | X                      |
| Walking capacity                             | 6-minute walk test (6MWT)                    | X                                                                        | X                                 | X                      | X                      |
| Leg muscle endurance                         | 30-second sit to stand (30-sec-STS)          | X                                                                        | X                                 | X                      | X                      |
| Static and dynamic balance                   | Guralnic test (SPPB) and Timed-up-go (TUG)   | X                                                                        | X                                 | X                      | X                      |
| Muscle strength upper extremity              | Hand-grip strength (Jamar dynamometer)       | X                                                                        | X                                 | X                      | X                      |
| Data registrations and
expense indicators | Adherence to intervention/self-maintenance   |                                                                          | X                                 | X                      | X                      |
|                                              | Adverse events recorded                      |                                                                          | X                                 | X                      | X                      |
|                                              | Number of hospital admission                 | past 12-mo                                                               | X                                 | X                      | X                      |
|                                              | Length of stay – hospital admission          | past 12-mo                                                               | X                                 | X                      | X                      |
|                                              | Consultant visits                            | past 12-mo                                                               | X                                 | X                      | X                      |
|                                              | Mortality                                    |                                                                          | X                                 | X                      | X                      |
|                                              | Comorbidities                                | X                                                                        | X                                 | X                      | X                      |
| Descriptive variable                  |                                              |                                                                          |                                   |                        |                        |
| Lung function test                           | FEV1/FVC ratio in %                          | X                                                                        |                                   |                        | X                      |
|                                              | FEV1 (% predicted)                           | X                                                                        |                                   |                        | X                      |
|                                              | DLCO (% predicted)                           | if available                                                             |                                   |                        | if available           |
| Anthropometries                              | Body Mass Index (BMI)                        | X                                                                        | X                                 | X                      | X                      |
|                                              | Body weight (kg)                             | X                                                                        | X                                 | X                      | X                      |
|                                              | Body height (cm)                             | X                                                                        | X                                 | X                      | X                      |
|                                              | Fat Free Mass Index (FFMI)                   | if available                                                             | if available                      | if available           | if available           |
| Other information reported                   | Smoking status                               | X                                                                        | X                                 | X                      | X                      |
|                                              | Medication prescribed                        | X                                                                        | X                                 | X                      | X                      |
|                                              | Bone fractures                               | past 12-mo                                                               | X                                 | X                      | X                      |
| Qualitative data                      |                                              |                                                                          |                                   |                        |                        |
| Qualitative study                            | Interview
Survey
Observation           | Continuously during the recruitment, intervention and maintenance period |                                   |                        |                        |

| Table 2. Anticipated power on secondary outcomes – superiority to control |                                                                  |                                                                                                                                                                                                                                                                             |                                                                                                                                                                                             |                                                       |
|---------------------------------------------------------------------------|------------------------------------------------------------------|-----------------------------------------------------------------------------------------------------------------------------------------------------------------------------------------------------------------------------------------------------------------------------|---------------------------------------------------------------------------------------------------------------------------------------------------------------------------------------------|-------------------------------------------------------|
| Variables                                                                 | Instrument                                                       | Subscales                                                                                                                                                                                                                                                                   | Cronbach's alpha                                                                                                                                                                            | Hypothesized Difference/ SD (anticipated power)       |
| Anxiety and depression                                             | Hospital Anxiety and Depressions Scale (HADS)                    | HADS-A scale (0-21)
HADS-D scale (0-21)                                                                                                                                                                                                                                  | HADS-A 0.83
HADS-D 0.82                                                                                                                                                                  | HADS-A 1.5/2.5 (0.85)
HADS-D 1.5/2.5 (0.85)        |
| Health-Related Quality of Life                                     | EuroQoL 5-Dimension Questionnaire (EQ-5D)                        | EQ5D-questionnaire (mobility, self-care, usual activities, pain/discomfort, and anxiety/depression)
Norm based utility score (-0.624-1.000)
EQ5D-VAS (0-100 millimeters)                                                                                              | Not relevant – only one question in each dimension                                                                                                                                          | EQ5D-VAS 8/16 (0.81)                                  |
| Body pain- intensity and location                                  | Brief Pain Inventory (BPI)                                       | BPI-magnitude domain
BPI-inference domain
BPI-intensity (0-100 millimeter)                                                                                                                                                                                            | BPI-M 0.91
BPI-I 0.94                                                                                                                                                                    | BPI-intensity 2/4 (0.71)                              |
| Perceived mental and physical fatigue                              | Multidimensional Fatigue Inventory (MFI-20)                      | General fatigue
Physical fatigue
Reduced activity
Reduced motivation
Mental fatigue
Fatigue total score                                                                                                                                                      | GF 0.83
PF 0.85
RA 0.79
RM 0.82
MF 0.91                                                                                                                                         | Exploratory                                           |
| Perceived sleep-quality                                            | Pittsburgh Sleep Quality Index (PSQI)                            | Sleep Quality – component 1
Sleep Latency – component 2
Sleep duration – component 3
Habitual sleep efficiency – component 4
Sleep Disturbance – component 5
Use of sleep medication – component 6
Daytime dysfunction – component 7
Global PSQI score | Sleep Quality 0.57
Sleep Latency 0.45
Sleep duration 0.36
Sleep efficiency 0.46
Sleep disturbance 0.36
Sleep medication 0.28
Daytime dysfunction 0.25
Global PSQI 0.69 | Exploratory                                           |
| Physical activity                                                  | activePAL™ activity monitor (PAL Technologies Ltd., Glasgow, UK) | Steps per day
Minutes lying/sitting
Minutes standing/walking
Number of body transitions per day                                                                                                                                                                    | Not relevant                                                                                                                                                                                | Steps per day 1100/2262 (0.79)                        |
| Walking capacity                                                   | 6-minute walk test (6MWT)                                        | Distance in meter                                                                                                                                                                                                                                                           | Not relevant                                                                                                                                                                                | 26/44,5 (0.83)                                        |
| Muscle strength and endurance in legs                              | 30 seconds sit-to-stand test                                     | Total numbers of repetitions                                                                                                                                                                                                                                                | Not relevant                                                                                                                                                                                | 2.0/2.5 (0.98)                                        |
| Static dynamic balance                                             | Guralnic test, Timed up and go, 4-meter gait speed               | Time, seconds                                                                                                                                                                                                                                                               | Not relevant                                                                                                                                                                                | Not established
1.4/2.4 (0.83)
0.11/0.13 (0.99) |
| Hand-grip muscle strength                                          | Jamar hand-grip dynamometer                                      | Kilo                                                                                                                                                                                                                                                                        | Note relevant                                                                                                                                                                               | 5.0/7.3 (0.93)                                        |

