***Please read appendix 1. for information on the test procedure from the physical functioning test (Danish)***

## **3.6 Sample size and statistics**

*(performed by biostatistician [name], Clinical Research Centre, University Hospital Hvidovre)*

Three primary pairwise comparisons are made in the study, equivalence test between the two interventions and the superiority test for each intervention compared to the control group for the primary outcome of respiratory symptoms (COPD assessment test). Sample size estimation for the equivalence is based on a t-test with equivalence margin of -2.5 to 2.5 (clinically relevant difference), standard deviation (SD) of 4.5, power of 80% and significance level of 5%, and estimated 56 patients necessary in each group. For both, superiority tests a minimal clinical difference of 2.5, SD of 4.5, power of 80% and significance level of 5% were used in a two-sample t-test, with fixed sample of 56 patients in the intervention groups. This yields a necessary size of 36 patients in the control group. The sample size is increased by 25% in each group to account for expected withdrawal and loss of power from adjustment and thus a total of 185 (70/70/45) patients. Power estimations for all secondary outcomes are based on the decided inclusion of 185 patients, expected standard deviation and established minimal clinical important difference (MCID) (**Table 2**).

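### Table 2 gives two outcomes with the same standardised difference (0.50) powers of 0.81 and 0.71; at 70 vs 45 the EQ5D-VAS and steps-per-day powers are overstated by 7 to 8 points

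*Protocol*

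**What the plan says.** Protocol section 3.6 sizes the trial on the CAT score and arrives at "a total of 185 (70/70/45) patients". It then says: "Power estimations for all secondary outcomes are based on the decided inclusion of 185 patients", together with expected standard deviations and minimal important differences. The results are in "Table 2. Anticipated power on secondary outcomes – superiority to control", so the comparison is one intervention arm (70) against control (45).

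Each row prints the hypothesised difference, the SD and, in brackets, the power. Three rows matter most here:

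- Quality of life: "EQ5D-VAS 8/16 (0.81".
- Pain: "BPI-intensity 2/4 (0.71".
- Physical activity: "Steps per day 1100/2262 (0.79".

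No row carries its own sample size, alpha or sidedness. Section 3.6 names a two-sample t-test for the primary superiority comparisons, and sections 3.6 and 3.6.1 give a 5% level without saying whether it is one- or two-sided.

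**The concern.** For a two-sample t-test, power depends only on the standardised difference, the group sizes, alpha and sidedness. With one common basis, rows with equal ratios must have equal power, and a row with a smaller ratio cannot have a higher power. Table 2 breaks both rules. EQ5D-VAS and BPI share a ratio of 0.50 but differ by 10 points. Steps per day, at 0.486, is given 8 points more than BPI. That needs no assumption about the test.

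Quality of life and physical activity are both named in the primary objective (section 2.1.1). The table presents EQ5D-VAS and steps per day as having about 80% power. A reader who relies on it would expect more from these two comparisons than the stated inputs support.

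**Working it through.** **Inputs.** Group sizes 70 and 45, and the uninflated 56 and 36, are from section 3.6. The two-sample t-test is the one section 3.6 uses for the primary superiority comparisons. Alpha is 0.05, taken as two-sided (assumption). Differences and SDs are from Table 2.

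**Formula.** d = difference/SD; non-centrality = d × √(n1·n2/(n1+n2)); df = n1+n2−2; power = P(non-central t exceeds the critical t).

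**Worked case, EQ5D-VAS and BPI.** d = 8/16 = 2/4 = 0.500. n1·n2/(n1+n2) = 70·45/115 = 27.39 and its square root is 5.234. The non-centrality is 0.500 × 5.234 = 2.617. With df = 113 the critical t is 1.981, and the power is 0.737. The stated 0.81 is not reproduced, and neither is the stated 0.71.

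**Steps per day.** d = 1100/2262 = 0.486; non-centrality 2.545; power 0.713. The stated 0.79 is not reproduced.

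**All rows at 70 vs 45, two-sided:**

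| Row | d | Stated | Recomputed | Stated minus recomputed |
|---|---|---|---|---|
| EQ5D-VAS | 0.500 | 0.81 | 0.737 | +0.073 |
| Steps per day | 0.486 | 0.79 | 0.713 | +0.077 |
| BPI intensity | 0.500 | 0.71 | 0.737 | −0.027 |
| HADS-A, HADS-D | 0.600 | 0.85 | 0.876 | −0.026 |
| 6MWT | 0.584 | 0.83 | 0.858 | −0.028 |
| Timed up and go | 0.583 | 0.83 | 0.857 | −0.027 |
| 30-s sit-to-stand | 0.800 | 0.98 | 0.986 | −0.006 |
| Gait speed | 0.846 | 0.99 | 0.992 | −0.002 |
| Grip | 0.685 | 0.93 | 0.944 | −0.014 |

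**Could another single basis rescue the table?**

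- One-sided 5% at 70 vs 45: EQ5D-VAS 0.83 and steps 0.81, near the stated values. BPI would then also be 0.83 (stated 0.71) and HADS 0.93 (stated 0.85).
- Both interventions pooled, 140 vs 45, two-sided: EQ5D-VAS 0.83 and steps 0.81. BPI would again be 0.83.
- Uninflated 56 vs 36, two-sided: EQ5D-VAS and BPI 0.64, steps 0.615, HADS 0.79, 6MWT and timed up and go 0.77. Every stated power is higher than this.
- The best single two-sided pair of group sizes found in a grid search still leaves a largest error of 0.052.

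All rows fit to within 0.005 only if two bases are mixed. An example is 70 vs 40, with EQ5D-VAS (0.806) and steps (0.786) one-sided and the rest two-sided (BPI 0.705, HADS 0.851). That is a possible explanation, not something the protocol says.

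**Rounding of printed inputs.** At 70 vs 45 two-sided, BPI's 0.71 needs d = 0.484, which rounded inputs could give (1.94/4 = 0.485). EQ5D-VAS's 0.81 needs d = 0.547, reached only at the edge of rounding (8.5/15.5 = 0.548). Steps per day's 0.79 needs d = 0.533. Even 1150/2262 is only 0.508, so rounding does not rescue that row.

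**The case against.** The strongest reply is that the damage is narrow. Seven of the nine rows in the table above are at or slightly below their 70 vs 45 values, so they err on the cautious side. BPI's small gap may be rounding. Table 2 concerns secondary outcomes; it neither sets the sample size nor changes an analysis, and estimates with confidence intervals will carry the interpretation. All of this stands and limits the point to a table error.

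Sidedness is also a fair objection. The protocol does not state it, and its own CAT superiority calculation (2.5/4.5, 56 vs 36) gives power 0.73 two-sided and 0.83 one-sided, so the claimed 80% is met only one-sided. The replacement figures therefore depend on a choice that the protocol has not made. The contradiction between rows does not depend on it.

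A reader might infer that Table 2 ignores the planned attrition and that the true powers are those at 56 vs 36, about 0.61 to 0.64 for EQ5D-VAS, BPI and steps. The protocol does not support that. It discloses that the powers rest on the 185 to be included. Most rows lie below their full-enrolment values, so the figures do not show that losses were wholly disregarded. And the inflation has two purposes: "The sample size is increased by 25% in each group to account for expected withdrawal and loss of power from adjustment". No separate withdrawal rate is given, so 56 vs 36 is not a declared evaluable sample. It is also an unadjusted comparison, whereas section 3.6.1 plans mixed models that include the baseline value.

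**Conclusion.** The point holds for three rows. As printed, EQ5D-VAS at 0.81 and BPI at 0.71 cannot both be right for a ratio of 0.50, and steps per day cannot exceed BPI. On the stated 70 vs 45 basis, with a two-sided 5% t-test, EQ5D-VAS is 0.74 (overstated by 7 points) and steps per day 0.71 (overstated by 8 points). BPI is 0.74 (understated by 3 points).

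It would go too far to say that Table 2 as a whole fails. Sit-to-stand, gait speed and grip agree within 2 points, and HADS, 6MWT and timed up and go are understated by under 3 points. Nor can a cause be asserted. A mix of one-sided and two-sided calculations fits the numbers, but that is inference.

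The sizes rest on the two-sided assumption and on the printed differences and SDs. The inconsistency between rows rests only on the single basis declared in section 3.6 and on the inputs as printed.

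**What to change.** Recompute every row of Table 2 on one group size, alpha and sidedness, and state all three in the table heading. If the basis stays 70 vs 45 with a two-sided 5% test, the entries become:

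- EQ5D-VAS 0.74 (from 0.81), BPI 0.74 (from 0.71), steps per day 0.71 (from 0.79).
- HADS 0.88, 6MWT 0.86, timed up and go 0.86, sit-to-stand 0.99, gait speed 0.99, grip 0.94.

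If a one-sided test is intended, say so and apply it to every row. Where the printed difference or SD was rounded, print the value actually used.

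Optionally add a sensitivity column at the uninflated 56 vs 36: EQ5D-VAS and BPI 0.64, steps about 0.61, HADS 0.79, 6MWT and timed up and go 0.77 (two-sided). Label it as unadjusted and as covering withdrawal and adjustment loss together.

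The cost is a table correction. Two powers stated at about 0.80 fall below 0.75. The sample size, conduct and planned analyses do not change.
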